## Abstract

**Background:**

Though home-based human immunodeficiency virus (HIV) counseling and testing (HBHCT) is implemented in many sub-Saharan African countries as part of their HIV programs, linkage to HIV care remains a challenge. The purpose of this study is to test an intervention to enhance linkage to HIV care and improve HIV viral suppression among individuals testing HIV positive during HBHCT in rural Uganda.

**Methods:**

The PATH (Providing Access To HIV Care)/Ekkubo Study is a cluster-randomized controlled trial which compares the efficacy of an enhanced linkage to HIV care intervention vs. standard-of-care (paper-based referrals) at achieving individual and population-level HIV viral suppression, and intermediate outcomes of linkage to care, receipt of opportunistic infection prophylaxis, and antiretroviral therapy initiation following HBHCT. Approximately 600 men and women aged 18-59 who test HIV positive during district-wide HBHCT in rural Uganda will be enrolled in this study. Villages (clusters) are pair matched by population size and then randomly assigned to the intervention or standard-of-care arm. Study teams visit households and participants complete a baseline questionnaire, receive HIV counseling and testing, and have blood drawn for HIV viral load and CD4 testing. At baseline, standard-of-care arm participants receive referrals to HIV care including a paper-based referral and then receive their CD4 results via home visit 2 weeks later. Intervention arm participants receive an intervention counseling session at baseline, up to three follow-up counseling sessions at home, and a booster session at the HIV clinic if they present for care. These sessions each last approximately 30 min and consist of counseling to help clients: identify and reduce barriers to HIV care engagement, disclose their HIV status, identify a treatment supporter, and overcome HIV-related stigma through links to social support resources in the community. Participants in both arms complete interviewer-administered questionnaires at six and 12 months follow-up, HIV viral load and CD4 testing at 12 months follow-up, and allow access to their medical records.

**Discussion:**

The findings of this study can inform the integration of a potentially cost-effective approach to improving rates of linkage to care and HIV viral suppression in HBHCT. If effective, this intervention can improve treatment outcomes, reduce mortality, and through its effect on individual and population-level HIV viral load, and decrease HIV incidence.

**Trial registration:**

NCT02545673

## Background

In the fight against human immunodeficiency virus (HIV), efforts to expand access to antiretroviral treatment (ART) are being prioritized globally. ART has the ability not only to improve health outcomes for the individual, but also in the prevention of ongoing HIV transmission through reducing viral load (VL). The push towards universal access to ART is reflected in the United Nations Joint Programme on HIV/Acquired Immunodeficiency Syndrome (AIDS) “90-90-90” goals, which aim to get 90% of people living with HIV (PLHIV) aware of their status, 90% of those diagnosed linked to care and receiving HIV treatment, and 90% of those receiving treatment virally suppressed by 2020 [1]. The 2016 World Health Organization (WHO) consolidated guidelines recommend all PLHIV be started on ART immediately upon diagnosis, regardless of CD4 cell count or disease stage [2]. However, significant challenges in getting PLHIV linked to HIV care and on ART remain, including in sub-Saharan Africa (SSA), the region most affected by the HIV epidemic. It is estimated that only 53% of those eligible for ART in SSA were receiving it in 2015 [3]. Several systematic reviews of studies in SSA demonstrate low rates of linkage to care after HIV testing [4–7], with up to two-thirds of patients lost to follow up before initiation of ART [7]. Thus, strategies to facilitate linkage into HIV care in SSA are needed, especially as the number of people eligible for ART grows as countries implement “test and treat” recommendations throughout the region.

In Uganda, it is estimated that only 65% of the 1.46 million PLHIV were aware of their status in 2015, of which only 51% were receiving ART [8]. Moreover, the number of people eligible for ART is expected to increase, as the revised 2016 Ugandan Ministry of Health (MOH) national treatment guidelines, which take effect in 2017, promote expansion of ART to all PLHIV, and put forth a number of strategies to increase the number of people aware of their HIV status and on treatment [8]. Home-based HIV counseling and testing (HBHCT) is one such approach, where HIV counseling and testing teams travel door-to-door and offer HIV testing services. HBHCT is especially important in the era of expanded access to ART and “treatment as prevention,” since HBHCT, compared to other modalities of testing, identifies HIV infections at an earlier disease stage and reaches more people who have never had an HIV test [9]. Moreover, HBHCT may be the most cost-effective testing strategy per person tested [9] and per new HIV infection identified [10]. However, though HBHCT is being widely implemented throughout SSA, [11] very few studies have examined linkage to care and treatment for individuals who test HIV positive at home [12–14].

The most common linkage-to-care approach with HBHCT, paper-based referral to care sometimes with follow-up home visits, has not been rigorously evaluated, and a number of HBHCT-specific barriers may limit its effectiveness. A systematic review on linkage to care in developing countries identified the following as the most commonly cited barriers: psychosocial factors (fear of being seen at the clinic, fear of disclosing, not feeling sick), structural and economic barriers (transportation costs, distance to the clinic), and health system factors (drug stock-out) [5]. Research evidence in Uganda has similarly documented these barriers [15], with pervasive HIV stigma, especially in rural areas, a particularly prominent barrier to care [16–19]. Such barriers may limit implementation of HBHCT; while HBHCT minimizes stigma and structural barriers of HIV testing (e.g., transportation) by bringing the test directly to patients [20], such barriers may remain an issue for linkage to care, as testing occurs away from the health facility and in a community setting, where fear of stigma may be elevated. Moreover, there is less structure in place for tracking patients testing positive in HBHCT, which is often done once without any follow-up [21]. In Uganda, HBHCT has been shown to be highly acceptable; 94% of individuals offered testing in a district-wide HBHCT study accepted testing and received their results [22]. However, only 10.5% of those who tested HIV positive were linked to ART [22]. In another study, only 58% of those who tested positive in HBHCT were linked to care within 12 months [23]. In HBHCT studies across SSA, linkage ranges from 42% to 97% within 1-12 months follow-up [24–30].

Low rates of linkage to HIV care during HBHCT highlights the need for interventions aimed to improve access to HIV care and treatment for individuals testing HIV positive in the home. The literature on HBHCT programs suggests that those with two follow-up home visits with counseling have better linkage compared to those with one or no follow-up home visits [24–30]. This finding is supported by recent trials in South Africa and Uganda, which found lay counselor facilitation and follow-up visits increased linkage [14, 31]. Based on evidence of the strong influence of HIV stigma, linkage to care interventions should be optimized in the context of rural HBHCT if they are to effectively reduce HIV stigma while addressing other barriers to care. A review of interventions to reduce HIV stigma found those providing social support to PLHIV were effective at reducing stigma [32], and emotional support through support groups has been shown to reduce internalized stigma among HIV-positive women in South Africa [33]. While no intervention studies have further linked reductions in stigma to subsequent improvements in linkage to care, a randomized trial in Uganda showed that counseling and social support via home visits doubled the likelihood of linkage to care for newly-diagnosed PLHIV [34]. Other data similarly suggests that social support may increase care linkage and retention [35–37], as well as reciprocal relationships between social support and HIV stigma [38]. Thus, providing PLHIV social support soon after diagnosis may protect them from internalizing HIV stigma and buffer the effects of enacted HIV stigma, which in turn may improve linkage to HIV care.

This paper describes the protocol for a cluster-randomized controlled trial (CRCT) to test an enhanced linkage to care intervention during HBHCT in rural Uganda. Our Providing Access To HIV care (Providing Access to HIV Care (PATH)/ *Ekkub*o) intervention enhances a similar strategy tested by Coates, Wanyenze, Bangsberg, and colleagues [39] that was found to reduce time to HIV care and treatment among patients receiving opt-out HIV testing in health facilities in Uganda. The intervention facilitated linkage by: providing orientation to the HIV care system, counseling to help clients identify and reduce barriers to engagement in care, and assistance disclosing and identifying a treatment supporter. The PATH/Ekkubo intervention described in this paper enhances the original intervention in order to increase its impact on multiple outcomes, including HIV viral suppression, and adapts the intervention to address barriers specific to HBHCT by providing additional counseling with increased emphasis on HIV stigma reduction through increased social support. We test this intervention in a CRCT, with randomization at the level of the village rather than at individual level, to avoid potential contamination since village residents interact with one another regularly in our study setting. The specific aims are:Compare the efficacy of the enhanced linkage to care intervention (PATH) vs. standard-of-care (paper-based referrals) at achieving individual and population-level HIV viral suppression, and intermediate outcomes of linkage/time to care, time to/receipt of ART. We hypothesize that the PATH intervention study arm will have a higher proportion of participants who are: a) virally suppressed at 12-month follow up, and will have shorter time to: b) HIV care and c) ART initiation, among those eligible, than the standard-of-care study arm. We also hypothesize that the effect of the intervention on HIV viral suppression will be mediated by intermediate behavioral outcomes: linkage to care and ART initiation. Finally, at the cluster level, we hypothesize that villages randomized to the intervention arm will have higher rates of population-level HIV viral suppression than those in the standard-of-care study arm at 12-month follow-up.Using the standard-of-care group as a natural history control, collect longitudinal data on barriers to and facilitators of linkage to and retention in care and treatment and HIV viral suppression.Estimate the cost and cost-effectiveness of the intervention, as compared to standard-of-care HBHCT, in terms of: viral suppression, linkage to care, and receipt of ART.

## Design and methods

### Setting

The study is being conducted in the rural districts of Butambala, Mpigi, Mityana, and Gomba in central Uganda. Health services, including HIV care and treatment, are provided free at government health facilities. In line with WHO recommendations [40], the Ugandan MOH 2016 guidelines, now expand access to lifelong ART to all adolescents and adults living with HIV immediately upon diagnosis regardless of CD4 count, in contrast to their previous eligibility threshold of CD4 < 500 [8]. Our study began before these new guidelines were nationally disseminated and implemented. Under the currently implemented MOH protocol, at the first clinic visit, a CD4 test is done and patients are started on co-trimoxazole. Once CD4 results are available (<2 weeks), those eligible for ART receive pre-treatment counseling and are given an appointment to come back 1 week later to initiate ART. HIV care and treatment, as well as peer support groups for PLHIV, are available at all district hospitals and level III health centers. As the 2016 policy for the expansion of lifelong ART is rolled out during 2017 all HIV-positive individuals will become eligible for ART regardless of their CD4 count. Throughout Uganda, a cadre of lay workers, constituting the Village Health Team (VHT), support community health-related activities and serve as liaisons between the community and the health facilities.

### Study design

The trial design is a matched-pair two-arm, cluster-randomized design with clusters being villages. One arm is the PATH/Ekkubo intervention arm and the other is a standard-of-care (control) arm. Villages are randomized to study arms. We will include 40 villages with approximately 600 participants across all clusters (villages). We will conduct structured interviews at baseline (pre-intervention), and at six and 12-month follow-up. Similarly, blood draws for HIV viral load and CD4 testing will be done at baseline and at 12-month follow-up. The design is illustrated in the CONSORT Diagram, Fig. 1.

**Fig. 1 Fig1:**
[figure not shown]
Consort Diagram of the Study Design

### Study population

The study population is adults aged 18 to 59 as well as emancipated minors (which according to the Ugandan National Council for Science and Technology are those under 18 who are married, have children, or are pregnant), residing in villages selected for inclusion in the study. Individuals who have accepted HBHCT and provide written (or thumb-printed) informed consent will be eligible to participate in the study.

### Sampling and randomization

The sampling scheme is stratified clustering with matched-pair sampling. Within each district we will pair match the 40 clusters (villages) by population size and proximity to major and regional roads, since the latter may facilitate access to health services because of greater availability of transportation. Using computer generated random numbers, we will randomly assign one village to be in the intervention arm and the other to the standard-of-care arm. Since village residents interact with one another regularly, we chose to randomize at the level of the village instead of randomizing individuals to study condition to avoid potential contamination. We will ensure that villages assigned to different study conditions are not within 4 km (1 h. by foot) of each other.

### Procedures

#### Community mobilization for HBHCT

Following the Ugandan MOH guidelines [41], this study provides village-wide HBHCT across the study villages. HBHCT and study recruitment is being conducted over approximately 46 months, beginning in November 2015 and ongoing through August 2019. The HBHCT teams will work in two villages at a time (one village from each study arm), and proceed to the next two villages upon completion, and so on. Prior to beginning recruitment in a village, members of our research team will meet with political, religious, and other village leaders, and identify VHT members to will serve as “mobilizers;” together VHTs and community leaders will inform the residents about HBHCT and the upcoming study. Using existing lists of households and maps of homesteads within the village, VHT mobilizers will visit all households in the village and seek permission for the HBHCT team to visit. For the households who agree to have the team visit, the VHT will set an appointment for this visit. The VHT will accompany the team to the household on the scheduled visit day, introduce the team and then leave to allow the recruitment, informed consent, data collection, and HIV testing to occur. The teams will set appointments to re-visit households in which household members were absent. The HBHCT teams consist of a study interviewer, a laboratory technician, and an HIV counselor who were all previously trained in general research procedures. Additionally they were trained in the study protocol and procedures.

#### Eligibility, recruitment, and informed consent procedures

##### HBHCT and brief baseline questionnaire

After the team is introduced by the VHT during the HBHCT visit, the interviewer will verbally screen household members for eligibility for HIV testing and study participation using a brief questionnaire. Eligibility for the baseline interview includes being 18-59 years of age or an emancipated minor, accepting HIV testing, speaking Luganda—the predominant language spoken in the study area, or English and residing in the household. Individuals who don’t normally sleep in the house will be excluded because they may live outside of the study area). We will obtain written informed consent for conducting the baseline interview and HIV testing. Those who consent will be interviewed before being tested for HIV as it would be insensitive to ask participants to answer interview questions after learning they are HIV positive. We expect approximately 25,000 individuals will participate in this aspect of the study.

##### Intervention trial

Individuals who participated in the brief baseline questionnaire interview and are identified as newly diagnosed HIV positive by our HBHCT team, as well as individuals who disclose as being known to be HIV positive during the baseline questionnaire and are confirmed positive in re-testing by the HBHCT team, but have never linked to HIV care, will be eligible for participation in the intervention trial. Only one person per household will be included in the intervention trial to ensure independence in the data. Using computerized random selection, we will randomly select one of the eligible HIV-positive household members for inclusion in the intervention trial. For ethical reasons the same follow-up support (intervention or control) will be offered to other newly diagnosed or HIV-positive household members not in care as will be provided to the household member included in the intervention study. A total of approximately 600 participants (approximately 300 in intervention and 300 in control arm villages) who are eligible and provide written informed consent to participate in the intervention trial will be enrolled.

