##### CD4 and HIV VL testing only

We anticipate that approximately 700 participants who complete the baseline questionnaire and test HIV positive will be excluded from the intervention trial because they are already aware of their status and have linked to HIV care, or because there are multiple new HIV diagnoses within a household. These individuals will be offered participation in a “CD4 and VL testing only” group. Including this group will allow us to have HIV VL measures from all consenting new or known PLHIV in the included villages which provides us the ability to assess the population-level effects of the intervention. Study staff will obtain written informed consent for the collection of CD4, VL, and a brief questionnaire interview at 12-month follow-up. See Fig. 1 for a flowchart depicting the study procedures and sample size approximation per study arm.

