*HIV status* (baseline). Health workers will obtain a finger stick capillary blood sample to run the HIV rapid tests. Following WHO recommendations to assure HIV testing quality in high prevalence settings [43] and the Ugandan MOH recommended assays, the rapid HIV testing algorithm we will be using in the study is as follows: Determine HIV-1/2 Assay (Alere/ Abbott Laboratories, Chiba, Japan) as the first test in the algorithm. If Determine is non-reactive, an HIV-negative result will be reported. For those found reactive with Determine, a second test, HIV 1/2 STAT-PAK (Chembio Diagnostic Systems, Medford, NY, USA) will be performed. If reactive with STAT-PAK, results will be reported as HIV positive. If reactive with Determine and non-reactive with STAT-PAK, both the Determine and STAT-PAK tests will be repeated. If both the repeat Determine and repeat STAT-PAK are reactive, an HIV-positive result will be reported. If both the repeat Determine and repeat STAT-PAK are non-reactive, an HIV-negative result will be reported. If the repeat Determine is reactive and the repeat STAT-PAK result is non-reactive, the sample will be tested using Uni-Gold HIV (Trinity Biotech, Bray, Ireland). If Uni-Gold is reactive, an inconclusive result will be reported and the participant will be re-tested in 14 days. If Uni-Gold is non-reactive, an HIV negative result will be reported. For quality control purposes, a venous blood sample will be taken with every 10th participant who tests HIV negative. Deoxyribonucleic acid polymerase chain reaction tests will be performed on these specimens for quality control.

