*Receipt of instrumental and emotional social support* (six and 12 months). We will measure receipt of instrumental and emotional social support using the Social Support Scale [51], which contains six items on emotional support and four items on instrumental social support. This scale was adapted from the Duke-University of North Carolina Functional Social Support Questionnaire [52] and has been validated among PLHIV in rural Rwanda (α = 0.91) [53]. In addition, we will determine if participants have a treatment supporter, have attended HIV support groups, or been counseled by an HIV-positive peer educator, and how helpful each of these forms of counseling have been on a four point scale ranging from “not helpful” to “very helpful.”
*HIV stigma* (baseline, six, and 12 months). At baseline, for those individuals reporting they are HIV negative or do not know their HIV status, we will measure enacted stigma, including nine items on discrimination, stereotypes, and prejudice using Kalichman et al.’s [54] AIDS-related stigma scale, which has been validated in South Africa [54]. We will also measure anticipated stigma, asking participants how they would feel if they tested positive, using six items from Earnshaw’s [42] anticipated stigma scale and six items from Berger et al.’s [55] HIV stigma scale. We will calculate the mean of all participants from each village to get a village (cluster)-level HIV stigma score at baseline. At six and 12-month follow up, and at baseline for those who report already knowing they are HIV positive, we will assess the following dimensions of HIV stigma among PLHIV [56]: (a) anticipated stigma using six items from Earnshaw’s [42] anticipated stigma scale and two subscales from Berger et al.’s [55] HIV stigma scale: eight items assessing anticipated stigma related to disclosure and eight items assessing anticipated stigma related to concern with public attitudes about PLHIV; (b) enacted stigma using six items from Earnshaw’s scale [42], 16 items from the personalized HIV stigma subscale of Berger et al.’s [55] scale, as well as items from Sayles et al.’s [57] multidimensional HIV stigma scale: 12 items from the stereotypes subscale and seven items from the social relationships subscale; and (c) internalized stigma using Kalichman et al.’s [58] internalized AIDS-related stigma scale. All of these measures have shown good reliability among sub-Saharan African samples (α = 0.73-0.78) [59–61].

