### Data analysis approach

Univariate statistics will be conducted on primary and secondary endpoints as well as covariates to describe the sample characteristics for the two study arms. Attrition in the two arms will be compared. Multiple imputation technique will be implemented and sensitivity analysis will be conducted.

To assess the primary outcome (the proportion of participants who are virally suppressed at 12-months) and secondary outcomes (linkage to care, time to care, receipt of opportunistic infection prophylaxis, and initiation of ART among those eligible for ART at baseline), linear mixed models and nonlinear mixed models will be applied. Information criterion such as Akaike information criterion or Bayesian information criterion will be used for model selection.

In evaluating the intervention effectiveness mechanisms, and mediators and moderators, we will use structural equation modeling to estimate the causal effects using growth mixture modeling to account for the longitudinal and clustered data. To assess an existence of moderators of an intervention effect, covariates such as disclosure, social support, HIV stigma, adherence, distance from the clinic, CD4 count, having other HIV-positive household members, number and duration of intervention sessions received, village-level stigma towards PLHIV, etc. will be included. A nonlinear mixed model will be fitted independently for each covariate plus the treatment variable and an interaction term between the covariate and the treatment.

To examine the natural history of stages in the HIV care continuum, we will use the control group to identify barriers to and facilitators of linkage to care and treatment, retention, and viral suppression, potential predictors include: sociodemographics, HIV stigma, disclosure, etc. Stepwise forward selection method from both logistic regression model and general linear model will be used to identify potential significant predictors for our analyses. Predictors that are selected from the stepwise method will be included in our mixed models.

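### People already virally suppressed at entry can enrol as newly diagnosed and count as 12-month successes in either arm; the baseline viral load already drawn should define the primary suppression analysis

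*Protocol article*

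**What the plan says.** All references are to the protocol article.

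- **Order of events** (HBHCT and brief baseline questionnaire): "Those who consent will be interviewed before being tested for HIV".
- **Prior status is self-reported** (Independent variables): the baseline stigma items are given "for those individuals reporting they are HIV negative or do not know their HIV status".
- **Two entry routes** (Intervention trial). The first is people "identified as newly diagnosed HIV positive by our HBHCT team". The second is "individuals who disclose as being known to be HIV positive during the baseline questionnaire and are confirmed positive in re-testing", provided they have never linked to care. As written, the never-linked condition attaches only to the second route.
- **Intended exclusion** (CD4 and HIV VL testing only): about 700 HIV-positive people are expected to be "excluded from the intervention trial because they are already aware of their status and have linked to HIV care", or because a household has several new diagnoses.
- **Primary outcome** (Data analysis approach): "the proportion of participants who are virally suppressed at 12-months". No baseline viral load condition is attached.
- **Baseline viral load** is drawn at the home testing visit from every trial participant (HIV testing procedures; Data collection procedures and measures). Primary outcome measures also says that change in viral load will be examined.
- **Clinic records** are abstracted as a secondary source for some outcomes (Data collection procedures and measures). No check of a new diagnosis against these records, treatment exposure or baseline viral load is stated.

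**The concern.** In effect, newly diagnosed means tested positive without having reported a known status. A person already on ART who does not mention it meets that definition, although the article intends such people to be outside the trial. If they stay on treatment they are suppressed at entry and at 12 months, and are scored as successes whichever arm their village is in. A linkage intervention cannot change their result.

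Three things follow. The estimated effect moves away from the effect in people not in care. A chance difference between arms in the share already suppressed passes straight into the primary comparison, with only 20 villages per arm to even it out. And time from HIV testing to clinic enrolment, or to ART initiation, is negative or undefined for these participants, so linkage and ART events can be credited that happened before the trial.

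**Working it through.** **Inputs from the article** (Sample size justification and power analysis): 55% v 75% suppressed, two-sided 5% type I error, 80% power, mean cluster size 14, attrition 18%, coefficient of variation k = 0.24, 40 clusters. Analysed per village: m = 14 × 0.82 = 11.48.

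**1. Reproducing the plan's figure.** Matched-pair formula for proportions, per arm:

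c = 2 + (1.96 + 0.84)² × V / (p1 − p0)², with V = [p0(1−p0) + p1(1−p1)]/m + k²(p0² + p1²).

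- Within villages: (0.2475 + 0.1875)/11.48 = 0.0379.
- Between villages: 0.0576 × (0.3025 + 0.5625) = 0.0498.
- V = 0.0877, so c = 2 + 7.85 × 0.0877/0.04 = 19.21. This rounds up to 20 per arm, 40 in all, as stated.

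The same section also mentions a 12% difference. That does not give 40 (55% v 67% needs 47.8 per arm), so the 20-point contrast is used here.

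Power with 20 pairs, keeping the formula's 2 extra clusters: Φ[d × √(18/V) − 1.96]. At 55% v 75% this is Φ(2.865 − 1.96) = 82%.

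**2. Dilution.** Let a share f in each arm be suppressed at entry and remain so. Then p' = f + (1−f)p, and the difference becomes (1−f) × 20 points. f is an assumption.

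**3. Power, three ways.**
- *Spread scaled*: the between-village SD shrinks by (1−f). This follows if f is equal across villages, since the always-suppressed then add no between-village variation.
- *k fixed*: k = 0.24 is applied to the diluted proportions, so the between-village SD rises with f.
- *Restricted*: people suppressed at baseline are left out, the contrast stays 55% v 75%, and m becomes 11.48 × (1−f).

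| f | Diluted rates | Difference | Power, spread scaled | Power, k fixed | Power, restricted |
|---|---|---|---|---|---|
| 0 | 55% v 75% | 20 | 82% | 82% | 82% |
| 5% | 57.3% v 76.3% | 19 | 80% | 77% | 81% |
| 10% | 59.5% v 77.5% | 18 | 79% | 72% | 80% |
| 20% | 64% v 80% | 16 | 75% | 60% | 78% |

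Worked row, f = 10%:
- Scaled: V = (0.2410 + 0.1744)/11.48 + 0.81 × 0.0498 = 0.0765.
- k fixed: V = 0.0362 + 0.0576 × (0.595² + 0.775²) = 0.0912.
- Restricted: V = 0.435/10.33 + 0.0498 = 0.0919, with d = 0.20.

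**4. Unequal f.** Suppose there is no true effect, 55% suppressed among the rest, and f = 5% in one arm and 15% in the other. Rates are 0.05 + 0.95 × 0.55 = 57.25% and 0.15 + 0.85 × 0.55 = 61.75%, a spurious 4.5 points. With a true 20-point effect, the same imbalance gives 21.5 points if the larger share is in the intervention arm and 14.5 points if it is in the control arm.

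**5. How large might f be?** Illustration only. Treat all of the roughly 700 excluded people as aware and linked (the article's figure also includes extra new diagnoses within a household). If a proportion d of in-care people stay silent, 700 × d/(1−d) are hidden: 37 at d = 5%, 175 at d = 20%. If 80–90% of them are suppressed and all enrol, they are about 5% and 23–26% of 600.

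**6. False-positive rapid tests.** Two reactive rapid tests suffice for a positive report, and the described laboratory quality control covers negatives only: "a venous blood sample will be taken with every 10th participant who tests HIV negative". With about 25,000 tested and 600 + 700 = 1,300 positive, some 23,700 are negative. An assumed algorithm specificity of 99.99%, 99.9% or 99.8% gives about 2, 24 or 47 false positives (0.4%, 4% or 8% of 600). These are upper figures, since not all would be selected or consent.

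**The case against.** **Power.** A reader might infer that hidden treatment badly underpowers the trial. That reading needs k to stay at 0.24 on the diluted proportions, which makes villages vary more as people with a constant outcome are added. If their share is similar across villages the spread shrinks instead, and restricting the analysis gains only about 1 to 3 power points. This objection stands. A larger loss would need f itself to vary between villages, and nothing in the article quantifies that.

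**Frequency.** A reader might take the Background's "fear of being seen at the clinic, fear of disclosing, not feeling sick" as evidence that people on ART conceal it from testers. It is listed there as barriers to linkage, so it makes silence plausible but does not show how common it is. Some features also reduce the incentive to conceal: people interviewed at baseline are not told of the trial, and joining means consenting after the result and accepting home visits and medical record access. This stands: the article shows that such people can enter, not how many do.

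**Baseline data.** It would be too strong to say that baseline viral load goes unused. Change in viral load is examined, and someone already below 20 copies/mL cannot show a 0.5 log10 reduction. But that analysis does not alter the proportion suppressed at 12 months.

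**Estimand.** Analysing everyone enrolled is a valid comparison of those a home-testing programme would refer, and with equal f it errs toward no difference. That is a fair reason to keep it in the report. It does not match the stated wish to leave out people already in care.

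**Analysis-plan detail.** Handling of pre-dated clinic records could be left to a plan not shown. The entry rule and the primary outcome, however, are both fixed in the article, and it is their combination that admits these people.

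**Conclusion.** The point holds as a flaw in how the entry rule and primary outcome combine. People already suppressed on ART who do not disclose can be enrolled and scored as successes in either arm. The contrast shrinks by (1 − f), to 19–16 points for an assumed f of 5–20%, and an imbalance in f can bias the result in either direction (4.5 points in the 5% v 15% example).

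The power cost is modest if between-village spread shrinks with f, and substantial only if k is held at 0.24. False positives are a minor addition whose size rests on an assumed specificity. The case for change therefore rests mainly on estimating the effect in the intended population and on protection from chance imbalance across 20 villages per arm. All sizes take the article's 55% and 75% (stated for those eligible for ART at baseline) as the rates in people not yet suppressed.

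**What to change.** - **Suppression.** Define the primary suppression analysis as enrolled participants whose sample from the home testing visit is not already suppressed at the threshold used for the primary outcome. Report all enrolled participants alongside, with the number and percentage suppressed at baseline by arm.
- **Linkage, time to care and ART initiation.** Use the abstracted clinic records to flag enrolment or ART dates before the home testing date, and do not count these as events.

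The baseline sample is drawn at the testing visit, before counselling can change viral load, so selecting on it does not condition on an effect of the intervention. It does not remove differences between arms in who consents, since consent follows both village allocation and the test result. Reporting baseline suppression by arm makes one part of that visible. The same restriction removes false positives, who would have undetectable virus.

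Cost: wording and derived flags from data already collected, with no new tests. The primary set becomes somewhat smaller (about 10.3 or 9.2 analysed per village rather than 11.5 at f = 10% or 20%) and loses some people who control the virus naturally.
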